### Aims and hypotheses

The present study involving patients with CKD was designed with 4 main objectives: (1) to assess the effects of dialysis on sleep parameters and determine the prevalence and severity of sleep disorders; (2) to determine the behaviour of sympathetic and parasympathetic autonomic nervous system activity through an analysis of heart rate variability; (3) to detect upper airway collapsibility as a risk indicator for OSA; and (4) to evaluate levels of depression, anxiety, stress and quality of life. Our hypothesis is that the weather weight gain due to volume overload observed during interdialytic period will influence the degree of collapsibility of the upper airway due to narrowing and predispose to upper airway occlusion during sleep, and to investigate the effects of nocturnal hemodialysis compared to daytime hemodialysis and the influences in the physiological variables of sleep, autonomic nervous system (ANS), and respiratory mechanics and thereby compromise the quality of life in chronic kidney diseases and end-stage renal disease patients undergoing dialysis.

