### Randomization

After the initial assessment and compliance with eligibility criteria, participants will be randomized into two intervention group [patients achieving diurnal hemodialysis and nocturnal hemodialysis] and the control group [CKD not submitted to dialysis]. Randomization numbers will be generated using a randomization table at a central office. A series of numbered, sealed, opaque envelopes will be used to ensure confidentiality. Each envelope will contain a card stipulating to which group the subject will be allocated.All patients underwent randomization protocol that will meet the eligibility criteria and be clinically stable.

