### Sample size calculation and statistical analysis

According to the findings of a previously published epidemiological study [17] that the proportion of adults with an apnea/hypopnoea index (AHI) ≥ 15 corresponds to 16.9% of the Brazilian population and that of a previous study [18] that AHI ≥ 15 had an approximately 50% prevalence rate in patients with CKD undergoing conventional dialysis (3 times a week, 4 h per session) [19], the sample size was calculated as 57 patients, with an *α* = 0.05 and *β* = 90% (test power).

The Kolmogorov–Smirnov normality test will first be performed to determine whether a normal distribution sample is present. A descriptive analysis will be performed, with the data expressed as either mean and standard deviation or median values and 95% confidence intervals, as appropriate. One-way analysis of variance will be used for comparisons between work shifts once the samples have a normal distribution. V_0.2_ and ΔV (%) values will be linearly correlated with the AHI, for which either the Pearson or Spearman correlation test will be used, depending on the sample distribution. Either the non-paired Student *t* test or Mann–Whitney test will be used for comparisons between individuals with and those without OSA.

In addition, a logistic regression analysis of continuous factors with categorical responses will be performed. Receiver operating characteristic (ROC) curves will be constructed to determine the sensitivity (true-positive rate) versus 100% specificity (false-positive rate) at various levels of the measured $\Delta \dot{V}$ (%) and V_0.2_ (%) to identify the cut-off value yielding the largest number of correctly classified patients. The statistical analysis will be performed by an experienced statistician using the JMP version 8.0 (SAS/STAT® Software, SAS Institute Inc., Cary, NC, USA) and SPSS version 16.0 programs (Somers NY). A 5% level of significance and 95% confidence interval will be applied.

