## Discussion

CKD is a major public health problem worldwide, and its incidence has increased in part by the increased life expectancy and increasing number of cases of diabetes mellitus and hypertension. Sleep disorders are common in patients with renal insufficiency and is much more prevalent in patients with end-stage renal disease than in the general population [4].

Symptomatic obstructive sleep apnoea syndrome has been related to be a risk factor for hypertension, heart failure and vascular dysfunction, and has been proposed to be causally related to both non-fatal and fatal coronary and cerebrovascular events [43]. Moreover, renal chronic patients frequently presented restless legs syndrome that also is associated with higher mortality and elevated incidence of cardiovascular events [44]. Thus, once presence of OSA also seems to reduce quality of haemodialysis [45] it’s incorrectly identification among CKD patients may lead to worst outcomes or fail of hypertension control [46].

Our hypothesis is that the weather weight gain due to volume overload observed during interdialytic period will influence the degree of collapsibility of the upper airway due to narrowing and predispose to upper airway occlusion during sleep, and to investigate the influences of different shifts haemodialysis in the physiological variables of sleep and ANS activity, and respiratory mechanics, and depression, anxiety, stress and quality of life in end-stage renal disease patients. With our proposed study, we intend to identify the main factors that cause sleep disorders in patients with CKD that lead to the identification of the best treatment to reduce mortality and improve the quality of life of these patients.

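### The collapsibility–AHI correlation and the OSA versus no-OSA tests ignore treatment group, so a significant pooled result may reflect a group difference; a group-adjusted analysis should stand beside them

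*Protocol article*

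**What the plan says.** Under Randomization, the protocol article builds the sample from three groups. Participants are to be "randomized into two intervention group [patients achieving diurnal hemodialysis and nocturnal hemodialysis] and the control group [CKD not submitted to dialysis". The allocation ratio is not given.

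Under Aims and hypotheses, the third of four main objectives is "to detect upper airway collapsibility as a risk indicator for OSA". The Discussion goes further: "we intend to identify the main factors that cause sleep disorders in patients with CKD".

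Under Sample size calculation and statistical analysis, four analyses bear on that objective:

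- The V0.2 and flow-drop "values will be linearly correlated with the AHI, for which either the Pearson or Spearman correlation test will be used".
- By OSA status, an unpaired t test or "Mann–Whitney test will be used for comparisons between individuals with and those without OSA".
- A logistic regression, described only as relating continuous predictors to categorical outcomes. Group is not named as a factor.
- ROC curves for V0.2 and flow drop, not split by group.

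The only analysis that uses group is the one-way ANOVA between shifts, and it does not address the link between collapsibility and OSA. The Polysomnography section gives every patient a sleep study, so AHI and OSA status exist in all three groups. The NEP test section places that test around haemodialysis sessions and does not say how it is timed in controls.

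**The concern.** If dialysis group shifts both OSA severity and a second variable, the two are correlated in the combined sample even when they are unrelated within every group. A bivariate correlation or a two-sample test by OSA status cannot tell this apart from a link between a patient's own airway collapsibility and that patient's own OSA.

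The protocol itself expects such shifts. Its planning figures set AHI ≥ 15 in about 50% of dialysed patients against 16.9% in the reference population. Its hypothesis has interdialytic fluid gain acting on both collapsibility and airway occlusion in sleep. The mix of dialysed and non-dialysed patients is also fixed by the allocation, so the pooled association describes no particular clinical population.

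At stake is how a positive finding on objective 3 may be worded: as a marker that works among patients of the same dialysis status, or as a restatement that dialysed and non-dialysed patients differ.

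**Working it through.** **Inputs from the protocol article.** Total 57; two-sided 5% tests assumed; AHI ≥ 15 about 50% on dialysis; reference rate 16.9%, which is a general-population rate.

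**Assumptions.** Allocation 1:1:1, so 38 dialysed and 19 not. The OSA rate in non-dialysis CKD is not given: 16.9%, 30%, 40% and 50% are tried. The group difference *d* in the second variable is not given: 0.5 to 0.96 SD is tried. The two dialysis groups are treated as alike. There is no association within any group.

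**The plan's own figure.** The usual two-proportion formula for 16.9% versus 50% at two-sided 5% and 90% power gives 41 per group (82 in total), not 57. That is a separate matter. Here 57 is taken as stated.

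**Step 1: make-up of the OSA groups.** At a control rate of 16.9%:

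- P(OSA) = 2/3 × 0.50 + 1/3 × 0.169 = 0.390, or about 22 of 57 patients.
- Share on dialysis among those with OSA = 0.333/0.390 = 85.5%.
- Share on dialysis among those without = 0.333/0.610 = 54.6%.
- Difference = 0.309, so about 31% of any dialysis-group difference in a measure carries over into the OSA comparison.

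At 40%, P(OSA) = 0.467, the shares are 71.4% and 62.5%, and only about 9% carries over.

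**Step 2: correlation created by group alone.** Treat AHI as a latent normal variable with shift Δ = z(0.50) − z(0.169) = 0.958 SD. With dialysis share π = 2/3, π(1−π) = 0.222 and

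r = dΔπ(1−π) / √[(1 + d²π(1−π))(1 + Δ²π(1−π))]

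- d = 0.5: 0.1065/√(1.0556 × 1.2040) = 0.094
- d = 0.96: 0.204/1.204 = 0.17

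**Step 3: how often the tests are significant (simulation, n = 57).** Pooled Pearson:

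| Control OSA rate | d = 0.5 | d = 0.8 | d = 0.96 |
|---|---|---|---|
| 16.9% | 11% | 19–20% | 24–25% |
| 30% | 7% | 10% | 11–12% |
| 40% | 5% | 6% | 6% |
| 50% | 5% | 5% | 5% |

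Spearman is similar. The t test by OSA status gives 9%, 13% and 17% in the first row, 6–10% at a control rate of 30% for shifts of 0.5 to 1.0 SD, and 5–6% at 40%; Mann–Whitney is close to it. With a term for dialysis status, all stay at about 5%.

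**Step 4: cost of adjusting.** With a true within-group correlation of 0.4, a 0.5 SD group shift in the same direction and a control rate of 16.9%, power for the correlation is about 88% adjusted and 95% pooled. With no group shift in the NEP measure it is 87% adjusted and 80% pooled.

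**The case against.** **Pooling is inferred.** The article never says that the groups are combined. Because the NEP test is described only around dialysis sessions, a correlation in dialysed patients alone is a live reading. This stands in part. On that reading only diurnal and nocturnal patients are pooled in the NEP analyses, the article gives no OSA figures for that contrast, and the table above does not apply to them. For the comparisons by OSA status of variables other than NEP, pooling remains the plain reading, since all patients have polysomnography and no group is excluded.

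**A marginal association is a legitimate target for a marker.** This stands. When group shifts both variables, the pooled null hypothesis really is false, and rejecting it is a true statement about the mixture. The percentages in the table are therefore not type I errors of the pooled test. They show how often it would be significant with nothing present within groups. The pooled result deserves reporting, but not the reading that collapsibility marks OSA at a given dialysis status.

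**The trial's hypothesis predicts a within-group link too.** Fluid gain can vary between patients in the same group, and part of a pooled association may be real. This is fair, and it is the reason to report both results. Adjustment leaves the within-group link in place.

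**The size rests on a favourable input.** This stands. The 16.9% is not a rate for non-dialysis CKD, and at 40% or more the effect nearly vanishes.

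**A condensed article leaves covariates to the full plan.** In general it does. Here, however, the named tests are of a form that carries no group term.

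A reader might also infer that objective 3 must get the wrong answer, or that pooling will hide a true link. The documents do not support either. The first needs sizeable shifts in both variables. The second needs a group shift opposite to the true association, against the direction that the protocol hypothesises.

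**Conclusion.** The concern holds as a worthwhile improvement, not as proof that the analysis fails. As written, the correlation and the OSA-status tests take no account of group, in a design where the protocol expects group to matter for both variables. A significant pooled result cannot separate a link among comparable patients from a group difference.

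With no within-group link, the pooled correlation would be significant in about 11–24% of trials at a control OSA rate of 16.9%, 7–12% at 30% and 5–6% at 40%, for group shifts of 0.5 to 0.96 SD. These figures assume 57 patients, 1:1:1 allocation and control patients who contribute NEP data. None of the control OSA rate, the NEP shift or the allocation ratio is given in the article, so the size could be anything from negligible to substantial. Quoting the upper end alone as an established false-positive rate would go beyond the documents.

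**What to change.** In Sample size calculation and statistical analysis, keep the pooled analyses and add a group-adjusted version of each, with group as control, diurnal or nocturnal:

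- a partial Pearson or Spearman correlation of V0.2 and flow drop with AHI, given group;
- a linear model with group, or a van Elteren test stratified by group, for comparisons by OSA status;
- group as a factor in the logistic regression.

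State that any claim that collapsibility indicates OSA independently of dialysis status rests on the adjusted result, and that the pooled result is reported as the marginal association. State also whether controls contribute NEP values to these analyses.

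The cost is wording and two degrees of freedom. Group is already recorded, so no new data or patients are needed. If the group shift runs in the same direction as a true association, some power is given up: about 88% against 95% for the correlation in the case worked above. The loss for the comparison by OSA status is not quantified here and may be larger.

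### Apart from the two airway-collapsibility measures, continuous factors are set only against OSA yes/no; at 57 patients this costs about 15 to 20 points of power for an assumed moderate correlation

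*Protocol article*

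**What the plan says.** All the analysis text is in the protocol article, under Sample size calculation and statistical analysis. Three analyses there link measured factors to sleep apnea.

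- **Full-scale AHI, two measures only.** V0.2 and flow drop "values will be linearly correlated with the AHI, for which either the Pearson or Spearman correlation test will be used", depending on the distribution.
- **OSA as two groups.** A t or Mann-Whitney "test will be used for comparisons between individuals with and those without OSA". The AHI cut that defines OSA is not given in that sentence.
- **Logistic regression.** "In addition, a logistic regression analysis of continuous factors with categorical responses will be performed". Neither the response nor the factors are named.

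ROC curves for V0.2 and flow drop follow. An AHI cut of 15 appears only in the sample-size text, which gives "corresponds to 16.9% of the Brazilian population" for the general population and "AHI ≥ 15 had an approximately 50% prevalence rate in patients with CKD undergoing conventional dialysis" for dialysis, and concludes that "the sample size was calculated as 57 patients".

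The Clinical evaluation section lists many more continuous factors: BMI, neck, waist and hip circumferences, heart rate variability, maximum ventilatory pressure, laboratory values and questionnaire scores. The Discussion states the purpose: "we intend to identify the main factors that cause sleep disorders in patients with CKD".

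**The concern.** Under the Polysomnography section every patient has an overnight study, so AHI is available as a count per hour for all of them. An analysis that keeps only OSA yes/no treats a patient just above the cut like one with very severe disease, and a patient just below it like one with no events.

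For the two collapsibility measures, the correlation with AHI makes up for this. For every other continuous factor, no analysis that keeps the AHI scale is stated, and none is stated for any model with several factors. With a small sample, moderate associations would often be missed and those factors reported as unrelated to sleep apnea. A yes/no response also says nothing about how severity varies with a factor.

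**Working it through.** **Inputs from the document.** The sample is 57, and it is not said whether this is the total or per group; I take it as the total, analysed together. The OSA rate is 50% in dialysis patients and 16.9% in the general population, both for AHI ≥ 15. The significance level is 5%, taken as two-sided.

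**The plan's own figure.** The plan gives no power for these analyses. The 57 was derived for a proportion with AHI ≥ 15. It does not follow from the stated inputs: the usual two-sided comparison of 16.9% with 50% at 90% power gives 41 per group, 82 in total. That is a separate matter; 57 is used here only as the number of patients available.

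**Assumptions.** Log(AHI) is roughly normal and linearly related to a continuous factor with true correlation r. OSA prevalence is 50%, or 39% from (2/3)(0.50) + (1/3)(0.169) = 0.390. The 39% assumes three equal groups and controls at the general-population rate, neither of which the document states.

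**Step 1: information kept by the cut.** Cutting a normal variable at c, with proportion p above it, multiplies the correlation by k = φ(c)/√[p(1−p)].
- p = 0.50: k = 0.3989/0.5 = 0.798, k² = 0.637.
- p = 0.39: c = 0.279, k = 0.3837/0.4877 = 0.787, k² = 0.619.

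The asymptotic efficiency is therefore 0.62 to 0.64, so 36% to 38% of the information is discarded.

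**Step 2: power by formula.** Power ≈ Φ(atanh(r)·√(n−3) − 1.96), with √54 = 7.348. For r = 0.30:
- full scale: 0.3095 × 7.348 − 1.96 = 0.314, power 62%;
- cut at 50%: r becomes 0.30 × 0.798 = 0.239; 0.2441 × 7.348 − 1.96 = −0.166, power 43%.

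The loss is 19 points.

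**Step 3: power by simulation.** n = 57, 20,000 runs, 50% OSA:

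| r | Pearson, log AHI | t test, OSA yes/no | Loss | Spearman | Mann-Whitney | Loss |
|---|---|---|---|---|---|---|
| 0.20 | 32% | 22% | 10 | 30% | 22% | 8 |
| 0.25 | 48% | 33% | 15 | 44% | 31% | 13 |
| 0.30 | 63% | 44% | 19 | 58% | 42% | 16 |
| 0.35 | 77% | 57% | 20 | 73% | 55% | 17 |
| 0.40 | 88% | 70% | 18 | 84% | 68% | 17 |
| 0.45 | 95% | 81% | 14 | 92% | 79% | 14 |
| 0.50 | 98% | 89% | 9 | 97% | 87% | 10 |

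Losses are taken before rounding. At 39% OSA they are mostly one or two points larger.

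**Step 4: sensitivity.**
- *Prevalence.* For r from 0.25 to 0.41 the t-test loss is 18 to 25 points at 30% OSA and 23 to 35 at 16.9%.
- *Logistic regression, if its response is OSA at 50%.* Over the same r the loss is 12 to 19 points by likelihood-ratio test and 16 to 23 by Wald test.
- *Number of cases in that model.* 57 × 0.39 ≈ 22 to 57 × 0.50 ≈ 29, which supports few factors at once.
- *Skewness.* If AHI is lognormal (assumed log-SD 1) and left untransformed, Pearson gains only 2 to 4 points over the t test at a 50% split. The gain needs the log or rank scale.

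**The case against.** The strongest objection is that the logistic sentence names neither AHI nor OSA. It speaks of categorical responses in the plural, and the article defines other categories: Berlin risk, stress phase, anxiety band and Beck depression class. This stands as a caution. OSA status is the most natural reading, because the sentence comes between the OSA comparison and the ROC curves, but it is an inference. The two-group comparison names OSA outright, so the point does not rest on the logistic sentence alone.

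Second, the study's main hypothesis concerns airway collapsibility, and both collapsibility measures are already correlated with AHI on its full scale. This stands and limits the point to the other factors. A reader might infer that the plan dichotomises AHI in all its risk-factor analyses; the text does not support that.

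Third, the cut has a proper use. Objective 3 concerns collapsibility as a risk indicator for OSA, and ROC curves and prevalence need a binary status. This stands, and nothing here asks for the cut to be removed from those uses. Nor does the cut deprive objective 1 of its severity question, since description and the comparison between shifts need no cut.

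Fourth, a condensed article may leave model detail to an analysis plan that is not shown. That explains the unnamed response and covariates. It does not change which methods the article does state for these factors.

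Finally, 15 to 20 points might be read as a fixed cost of the plan. It is not: the document gives no correlation, no AHI distribution and no OSA cut for these analyses.

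**Conclusion.** The concern holds in a limited form. For continuous factors other than V0.2 and flow drop, the stated analyses are a with/without-OSA comparison and a logistic regression most naturally read as having OSA as its response. If those are the only analyses, power falls by about 15 to 20 points for a true correlation of about 0.25 to 0.43. This assumes 57 patients in all, OSA near 40-50% and log(AHI) roughly normal. Rank-based figures lie at or slightly below the lower end of that range in places. The loss is about 10 points at r = 0.20 or 0.50, smaller outside those values, and larger if OSA is less frequent.

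These are secondary association analyses and 57 was not sized on them. This is a worthwhile improvement in efficiency, not an error that invalidates the plan.

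**What to change.** Under Sample size calculation and statistical analysis, state that the main analysis of factors associated with sleep apnea is a linear regression of log(AHI+1) on the continuous factors, with V0.2 and flow drop included. If residuals remain skewed, use a rank-based or proportional-odds model of AHI. In the same sentences, name the response of the logistic regression and the AHI cut that defines OSA.

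Keep the with/without-OSA comparison, the logistic odds ratios, the prevalence and the ROC curves as clinical and diagnostic descriptions.

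The cost is one or two sentences, with no new data, visits or patients. The small downside is that the main effects are reported as ratios of AHI (strictly, of AHI+1) rather than odds ratios for OSA, which remain available as secondary results.

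### The NEP cut-off is the value that classifies most study patients correctly, so it follows the OSA prevalence of the recruited mix and its in-sample accuracy is optimistic

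*Protocol article*

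**What the plan says.** The third of the four main objectives (Protocol article, Aims and hypotheses) is "to detect upper airway collapsibility as a risk indicator for OSA". The section Sample size calculation and statistical analysis turns this into an ROC analysis of flow drop and V0.2: "curves will be constructed to determine the sensitivity (true-positive rate) versus 100% specificity (false-positive rate) at various levels of the measured" flow drop and V0.2, with the purpose "to identify the cut-off value yielding the largest number of correctly classified patients". The rule is thus stated: maximise the number classified correctly.

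Three further statements bear on it.
- Size: "the sample size was calculated as 57 patients". The article does not say whether this is the total or the number per group.
- Prevalence of AHI ≥ 15: the general adult figure "corresponds to 16.9% of the Brazilian population", and AHI ≥ 15 "had an approximately 50% prevalence rate in patients with CKD undergoing conventional dialysis". No figure is given for CKD without dialysis or for the whole sample.
- Composition (section Randomization): "participants will be randomized into two intervention group [patients achieving diurnal hemodialysis and nocturnal hemodialysis] and the control group [CKD not submitted to dialysis". No allocation ratio is given.

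The AHI level that defines OSA for the ROC curve is not stated.

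**The concern.** Counting correct classifications weights the two kinds of error by how often diseased and non-diseased patients occur in the sample. The same marker with the same discriminating ability then gets a different cut-off when the mix of patients changes. If dialysis patients and controls are pooled, that mix is partly a product of the design. A cut-off meant to indicate OSA risk in other CKD patients should not move with the number of controls recruited.

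Separately, a cut-off picked because it performs best in a small sample looks better there than it will in new patients. If the in-sample figures are quoted as the performance of the NEP test, they flatter it.

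At stake is the interpretation of objective 3. The comparisons between dialysis groups are not affected.

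**Working it through.** **The plan's own figure.** The article gives no expected AUC, sensitivity or accuracy, so there is no ROC figure to reproduce. Its 57 comes from comparing 16.9% with 50%. The usual two-sided 1:1 calculation at 90% power gives [1.96·√(2·0.3345·0.6655) + 1.2816·√(0.169·0.831 + 0.5·0.5)]² / 0.331² = 40.6, or 41 per group and 82 in total. The 57 is not reproduced, but that is a separate matter. Here 57 is taken as the size of the ROC sample.

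**Inputs.**
- From the article: the maximum-accuracy rule, n = 57, and prevalences of 16.9% and about 50%.
- Assumed: an equal-variance binormal marker, AUC 0.6 to 0.8, and OSA prevalence π from 30% to 60%. One value in that range, 39%, is what follows if two thirds of the sample have 50% and one third 16.9%: 2/3 × 50 + 1/3 × 16.9 = 39.0. Both the weights and the use of 16.9% for controls are assumptions.

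**Step 1: does the cut-off depend on prevalence?** Let non-cases be N(0,1) and cases N(d,1), with d = √2·z(AUC). The threshold that maximises accuracy is t = d/2 + ln((1−π)/π)/d. The Youden threshold is d/2 and contains no π. At AUC 0.7, d = 0.742 and d/2 = 0.371. Sensitivity is 1 − Φ(t − d) and specificity is Φ(t):

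| π | t | Sensitivity | Specificity |
|---|---|---|---|
| 30% | 0.371 + 0.847/0.742 = 1.513 | 0.22 | 0.93 |
| 39% | 0.371 + 0.447/0.742 = 0.974 | 0.41 | 0.83 |
| 50% | 0.371 + 0 = 0.371 | 0.64 | 0.64 |
| 60% | 0.371 − 0.405/0.742 = −0.176 | 0.82 | 0.43 |

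Youden gives 0.64 and 0.64 in every row.

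**Step 2: what happens with 57 patients?** In 3,000 simulated samples per setting, the cut-off was chosen in the sample and its true performance taken from the generating distributions. At AUC 0.7, mean true sensitivity under the plan's rule was about 29%, 43%, 63% and 78% at prevalences of 30%, 39%, 50% and 60%. Youden cut-offs estimated in the same way gave about 62% to 64% throughout. Estimated must be compared with estimated, because both rules are unstable at this size. At 39% prevalence the 5th to 95th percentile range of true sensitivity was about 9% to 77% under the plan's rule and 33% to 87% under Youden.

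**Step 3: how large is the optimism?** In-sample against true accuracy at 39% prevalence:

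| AUC | In-sample | True | Gap (points) |
|---|---|---|---|
| 0.6 | 67.3% | 60.0% | 7.3 |
| 0.7 | 72.1% | 65.1% | 7.0 |
| 0.8 | 78.1% | 72.1% | 6.0 |

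Over AUC 0.6 to 0.8 and prevalence 30% to 60%, the gap is about 5 to 9 points when the number of cases varies from sample to sample, and about 4 to 7 when it is held fixed. Youden cut-offs show a similar gap, about 5 to 7 points.

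**The case against.** A reader might infer that this rule will miss many OSA cases. The documents do not support that. It requires OSA to be the minority in the ROC sample, and the prevalence there is not given. The only dialysis figure is about 50%, where the rule and Youden agree. The NEP test section schedules the test before and after haemodialysis sessions, so it is unclear whether non-dialysis controls enter the ROC analysis at all. If they do, the general-population 16.9% may be too low for them: the Background puts sleep disorders of all kinds in CKD at 40% to 80%. A lower AHI threshold for OSA could push prevalence above 50%, and the error would then be excess false positives. All of this stands.

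It is also fair that optimism is not peculiar to this rule, that Youden buys sensitivity with specificity when OSA is the minority (at AUC 0.7 and 39% prevalence, specificity falls from about 0.80 to 0.64), and that a risk indicator is not necessarily a screening test in which sensitivity must come first.

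A reader might also infer that no validation is planned. The article mentions none, but it is condensed, and a bootstrap could sit in a document not shown. It does not say that uncorrected accuracy will be reported as the test's performance. The optimism point is therefore conditional on how the results are reported.

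What the objection does not remove is the criterion. It is written into the plan, and a validation step elsewhere would correct the optimism but not the dependence on prevalence.

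**Conclusion.** The concern holds as a criticism of a stated criterion. The chosen cut-off, and with it the balance of sensitivity and specificity, is set by the OSA prevalence of the sample. At AUC 0.7, true sensitivity moves from about 29% to 78% as prevalence goes from 30% to 60%, with no change in the marker. Accuracy read off the selection sample is about 5 to 9 points too high.

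These sizes rest on n = 57, an equal-variance binormal marker and AUC 0.6 to 0.8. If 57 is the number per group, the optimism would be smaller and the prevalence dependence unchanged. The direction of the error cannot be stated from the documents: missed cases below 50% prevalence, false positives above it, neither at 50%.

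The point touches one supplementary analysis serving objective 3. It should be corrected, but it does not threaten the group comparisons. The printed false-positive axis (100% specificity, where 100% minus specificity is meant, possibly a lost sign) and the choice of NEP occasion and body position are side points and do not carry the finding.

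**What to change.** Change the ROC paragraph in four respects.

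1. Make the AUC with its 95% confidence interval the main ROC result for flow drop and for V0.2.
2. Replace the count of correct classifications by a pre-specified criterion that does not depend on sample prevalence: the Youden index, or a minimum sensitivity fixed in advance. Give the reason for the choice.
3. Report sensitivity, specificity and accuracy corrected for optimism by bootstrap, repeating the cut-off selection in every resample. Changing to Youden alone would not remove the optimism.
4. State the AHI level that defines OSA for the curve and whether non-dialysis controls are included. In the same edit, name the NEP occasion and position used and correct the axis label.

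The cost is wording and a bootstrap; no further patients or measurements are needed. The price is that reported accuracy becomes several points less favourable and specificity may fall, as in the 0.80 to 0.64 example above.

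### No primary outcome or contrast is named among four unranked main objectives all tested at 5%, and no stated test uses the outcome that sized the trial

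*Protocol article*

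**What the plan says.** Under *Aims and hypotheses*, the protocol article says that the study "was designed with 4 main objectives". The first is "to assess the effects of dialysis on sleep parameters and determine the prevalence and severity of sleep disorders" and the second is "to determine the behaviour of sympathetic and parasympathetic autonomic nervous system activity". The third concerns upper airway collapsibility, and the fourth covers depression, anxiety, stress and quality of life. None is put ahead of the others.

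Under *Randomization*, "participants will be randomized into two intervention group" (daytime and nocturnal haemodialysis) and a control group with CKD not on dialysis.

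Under *Sample size calculation and statistical analysis*, the sizing uses AHI ≥ 15. The proportion with it "corresponds to 16.9% of the Brazilian population" in one source and "had an approximately 50% prevalence rate in patients with CKD undergoing conventional dialysis" in another. From α = 0.05 and 90% power, "the sample size was calculated as 57 patients".

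The same section then lists:
- one-way ANOVA between shifts
- correlation of V0.2 and flow drop with AHI
- t or Mann–Whitney tests of patients with OSA against those without
- logistic regression of categorical responses on continuous factors
- ROC curves for V0.2 and flow drop

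It ends: "A 5% level of significance and 95% confidence interval will be applied". The article designates no primary outcome, no primary contrast and no exploratory tier.

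**The concern.** Naming the primary outcome belongs in the protocol. Here the article does more than stay silent. It gives four domains equal rank as main objectives and attaches one significance level to all of them. Read as written, an isolated p < 0.05 on one questionnaire scale has the same standing as a result on the outcome that justified the sample size.

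Two things are at stake. First, the chance of at least one false-positive result across the trial has no stated bound. Second, the power statement is not attached to any planned test, because the proportion with AHI ≥ 15 is used for sizing and then dropped from the between-group analysis.

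**Working it through.** **1. The plan's own figure.** Inputs from the sample-size paragraph: p1 = 0.169, p2 = 0.50, α = 0.05, power 90%. Sidedness is not stated, so two-sided is taken first. The mean proportion is 0.3345.

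n per arm = [1.96 √(2 × 0.3345 × 0.6655) + 1.2816 √(0.169 × 0.831 + 0.50 × 0.50)]² / (0.50 − 0.169)²
= [1.308 + 0.801]² / 0.1096 ≈ 40.6, so **41 per arm** (82 for two arms, 123 for three).

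Continuity correction gives 47 per arm. One-sided testing gives 33, or 39 with correction. None of these is 57 per arm or in total. The article does not say which of the two 57 is. If it is the total over three equal arms (19 each; the allocation ratio is also unstated), the power of one pairwise comparison at these rates is Φ[(0.331 √19 − 1.308) / 0.625] = Φ(0.216) ≈ 59%. If it is per arm, the power is about 97%. The mismatch is a separate matter. It matters here because 57 cannot be tied to a particular contrast.

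**2. Which contrast does the sizing describe?** It sets a general-population rate against a conventional-dialysis rate. The randomised control group is patients with CKD not on dialysis, not the general population. For nocturnal against daytime, the sizing paragraph defines conventional dialysis as three sessions a week of 4 hours, and *Study interventions* gives both shifts that same frequency and duration. The calculation therefore supplies no assumed difference between the two dialysis arms.

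**3. False-positive risk across the trial.** Assume no true effects and K tests at two-sided 5%. If they are independent, the risk is 1 − 0.95^K. For equal correlation r between test statistics, it was simulated as P(max |z| > 1.96).

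The article gives neither K nor r. Two values of K were tried:
- **K = 4:** one test per objective, the most lenient reading.
- **K = 18:** sleep 3 (AHI, Epworth, Berlin), autonomic 2 (sympathetic, parasympathetic), collapsibility 2 (V0.2, flow drop), and mood and quality of life 11 (stress, anxiety, depression, eight SF-36 domains). 3 + 2 + 2 + 11 = 18, with one test each.

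| K | r = 0 | r = 0.3 | r = 0.5 |
|---|---|---|---|
| 4 | 18.6% | 17% | 16% |
| 18 | 60.3% | 51% | 40% |

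For independent tests the risk passes one half between K = 13 (48.7%) and K = 14 (51.2%).

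**The case against.** **The adjustment method may be in an SAP.** This stands. Multiplicity procedures are commonly left to the SAP, which is not shown, so the lack of one is not the finding. It does not cover the missing primary outcome: an SAP that picked one would have to override a published text that calls four objectives main.

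**The count of 18 is a reviewer's list.** This also stands. The article describes the eight SF-36 domains as the structure of the instrument and does not say that each is tested. Berlin is a risk classification, to which ANOVA would not apply. Several objectives are worded descriptively. The count also leaves things out: spirometry, ventilatory pressures, other polysomnography variables, seated and supine NEP, and measurements before and after dialysis. It can err in either direction, so a range is given.

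**Stronger readings the documents do not support.** A reader might infer that a chance positive finding is more likely than not. That needs no true effects, about 14 or more effectively independent tests, and low to moderate correlation. At r = 0.5 the 18-test figure is 40%, and one test per objective stays below 20%. A reader might also multiply the outcomes by three pairwise group contrasts. The section names one ANOVA between shifts, does not say whether the control group is in it, and states no pairwise or post-hoc tests.

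Nor does the 5% sentence say that any p < 0.05 will be claimed as a treatment effect. The OSA comparisons, correlations and ROC curves are association or diagnostic analyses. The logistic regression could take AHI ≥ 15 as its response, but its stated factors are continuous, so it is not a comparison of randomised groups.

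**Conclusion.** The point holds as a protocol-level defect: four unranked main objectives, a flat 5% level, no primary outcome or contrast, and a sizing outcome that no stated test compares between the randomised groups. The trial-wise error rate is uncontrolled. Under no true effects it is about 16–19% on the most lenient reading, already more than three times the nominal 5%. It is about 40–60% for an assumed 18 outcomes with correlation from 0.5 to 0. The count and the correlations are assumptions, so these are illustrations of scale rather than properties of the plan. The conclusion itself rests only on the text.

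**What to change.** 1. Designate the proportion with AHI ≥ 15 as the single primary outcome. It is the only outcome with a sizing basis. That basis does not carry over to AHI as a continuous measure.
2. Name one between-group contrast and its test at two-sided 5%.
3. Restate the sample size, or the achievable power, for that contrast with rates that apply to its two groups, and say whether 57 is per arm or in total. If nocturnal against daytime is chosen, a new assumed difference is needed.
4. Label all other outcomes, contrasts, correlations and ROC analyses secondary or exploratory, and give any multiplicity adjustment in the SAP.

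Most of this is wording, but step 3 is real work and may make the stated power less favourable. Secondary results just under 0.05 could no longer be claimed as confirmatory. Keeping four co-primary outcomes instead, one per objective, would cost more. Bonferroni gives 0.05 / 4 = 0.0125 each (overall 1 − 0.9875⁴ = 4.9%), and on the stated rates the AHI comparison would then need 56 per arm rather than 41.
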